### Statistical analysis

The results of this study for efficacy outcomes will be analyzed based on both intention-to-treat (ITT) and per-protocol (PP) approaches with a primary consideration for ITT results. A PP analysis will be performed secondarily. A safety analysis will be performed based on the safety group.

The ITT group will include participants who are randomized after satisfying the eligibility criteria and receive one study drug at least once and have post-dose evaluation data. The PP group will include participants who satisfy the following conditions among the ITT group: (1) those who completed all planned visits and (2) those who did not receive and use drugs or treatments that may affect the evaluation of efficacy during the study. The safety analysis group will include participants who received study drugs at least once and have post-dose safety evaluation data.

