**Fig. 1 Fig1:**
[figure not shown]
The clinical research flowchart

Once the volunteered participants have been included, researchers will explain the research procedures in detail and require them to sign a written informed consent form which is signed by the subjects or their legal representative. All participants can withdraw their consent at any time during the trial.

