### Design

This is a prospective, open-label, randomized controlled, multicenter clinical study with two arms. Eligible patients are first screened by safety laboratory testing. Patients with diagnosed mild/general COVID-19 infection are randomized to the following two arms at a 1:1 ratio:
Arm 1 (control arm): lopinavir/ritonavir treatment for diagnosed mild/general COVID-19 infection uses lopinavir 800 mg/day and ritonavir 200 mg/day for no more than 10 daysArm 2 (investigation arm): chloroquine phosphate treatment using chloroquine phosphate 1000 mg/day, equivalent to chloroquine 600 mg/day for no more than 10 days

The CRF is shown in Fig. 1. The schedule of treatment visits and data collection (also known as the CRF) is shown in Table 1.

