### Definitions

#### The clinical recovery time and adverse events

We define the clinical recovery time as the time (in hours, no more than 28 days) from the start of study drug intervention to normalization of body temperature, respiratory symptoms (cough, nasal stuffiness, nasal discharge, etc.), respiratory frequency, and blood-oxygen saturation. Specifically, also meeting the following criteria at the same time:
① No fever: axillary body temperature ≤ 37.2 °C② Relief of respiratory symptoms (72 consecutive hours)③ Respiration rate ≤ 24/min (resting state)④ Fingertip blood oxygen > 94%

Adverse events (AEs) refer to adverse medical events that occur after a patient or clinical trial participant receives a drug, but they are not necessarily causally related to treatment.

Serious adverse events (SAEs) refer to events that require hospitalization, prolonged hospital stay, disability, affect working ability, are life-threatening or fatal, cause congenital malformation and other events that occur during the clinical trial.

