### Randomization

Grouping is carried out using a centrally stratified, randomized block method. Before the trial, a statistical expert will use SAS software to set the number of centers at four, the block size will be four, the number of blocks will be 28, using a 1: 1 ratio between the experimental group and the control group, will generate 112 random numbers and corresponding grouping information. According to the haphazard allocation table used in advance, the statistical expert gives random numbers (1–112) in ascending order. Each random number and grouping information correspond to an envelope. The envelope is sealed and given to the researchers responsible for screening. Qualified subjects are selected, and the envelopes are received in the order of enrollment. After the envelopes are opened, the random-number and grouping information is removed, so that the subjects will be randomly assigned to the experimental group or the control group, and the corresponding treatment and observations performed. Each subject’s random number is unique and remains the same throughout the trial.

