### Sample size

The hypothesis of this study is that the use of chloroquine phosphate instead of lopinavir/ritonavir will increase the rate of throat-swab SARS-CoV-2 nucleic-acid negative conversion.

The main therapeutic index of this study is the clinical recovery time (after no more than 28 days), which is from the beginning of the study drug intervention treatment to the normalization of body temperature, respiratory symptoms, respiratory rate, and blood-oxygen saturation. In the later analysis, the log-rank method is used to compare the differences in clinical recovery time between the two groups of patients. The sample size of this study is calculated based on the log-rank method by using the log-rank test (Lakatos) (median survival time) module in the PASS 11.0 statistical software (see Additional file: Sample size report” for details).

Based on clinical experience [4, 18], the median clinical recovery time of the patients in the control group is expected to be 8 days, and the median clinical recovery time of patients in the experimental group can be shortened to 4 days (corresponding hazard ratio (HR) = 2.0) 112 patients (56 in each group) will be required to detect this difference with a significant level of *α* = 0.05 (both sides) with 85% confidence interval.

The trial is planned to be enrolled for 90 days, followed up for 28 days, and a final analysis is performed after 78 clinical recovery events occur. It is estimated that the drop-out rate of the experimental group and the control group is 5%.

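### The primary set labelled ITT is a treated-and-evaluable (modified ITT) set; in this open-label trial its exclusions can depend on the arm, with a possible but unquantified bias

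*Protocol article*

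**What the plan says.** Under Statistical analysis, efficacy is analysed by ITT and per protocol, "with a primary consideration for ITT results". The ITT group is defined as "participants who are randomized after satisfying the eligibility criteria and receive one study drug at least once and have post-dose evaluation data". The per-protocol group is a subset of that group. The safety group is "participants who received study drugs at least once and have post-dose safety evaluation data".

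Four other places bear on the point:

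- Design: "This is a prospective, open-label, randomized controlled, multicenter clinical study with two arms".
- Randomization: sealed envelopes are opened in order of enrolment. "After the envelopes are opened, the random-number and grouping information is removed", and the assigned treatment follows.
- Text under Fig. 1: "All participants can withdraw their consent at any time during the trial".
- Definitions: the primary time runs "from the start of study drug intervention to normalization of body temperature" and of the other recovery criteria. The Sample size section uses the same start.

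**The concern.** Meeting the eligibility criteria before randomisation is harmless as a condition. Taking a dose and having post-dose data are not, because both are settled after allocation. Under blinding, a one-dose rule can be defended because the exclusion cannot depend on the arm. Here patient and staff know the arm before the first dose. The Abstract and Background also record the investigators' view that the control drug had performed poorly (3/15 swabs improved, against 5/10 on chloroquine), so a preference between arms is plausible.

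If those who refuse or leave at once differ in prognosis between arms, the randomised comparison no longer protects the primary result, and the report would still call it ITT. The same set supplies the denominator of the treatment success rate. The safety set supplies the denominator of the SAE rate.

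**Working it through.** **1. The plan's own figure.** The point does not depend on the sample size, but the size can be reproduced. Inputs from Sample size: medians 8 and 4 days (HR 2.0), 90 days of enrolment, 28 days of follow-up, 5% drop-out, and alpha and power given as "0.05 (both sides) with 85% confidence interval", where I read 85% as power.

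- Schoenfeld: 4 × (1.960 + 1.036)² / (ln 2)² = 4 × 8.98 / 0.480, giving 75 events.
- Freedman: (1.960 + 1.036)² × (2 + 1)² / (2 − 1)² = 8.98 × 9, giving 81 events.
- Lakatos, the method the plan names, with 5% drop-out entered per day: 77.0 events and N = 110.2, in line with the stated 78 and 112. With 5% spread over 28 days, N is only about 81.

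**2. Who is left out.** An ITT set has 56 + 56 = 112 patients. The plan gives no rate of loss before a first dose or first evaluation. As an assumption only: if 5% were lost that early in each arm, 0.05 × 56 = 2.8, so about 53 + 53 = 106 would remain.

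**3. What exclusion can do to the log-rank test.** Simulation with no drug effect: exponential times, median 8 days in both arms, 56 per arm, censoring at 28 days, 4,000 trials per scenario. The Monte Carlo standard error near 5% is √(0.05 × 0.95 / 4,000) = 0.34 percentage points. HR above 1 favours chloroquine. The counts and patterns of exclusion are assumptions.

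| Excluded | Two-sided rejection | Estimated HR |
|---|---|---|
| None (all 112, fully followed) | 4% to 6% across runs | – |
| 6 at random, chloroquine arm | 4.5% | 1.00 |
| 3 per arm, from the slower half | 4.5% | 1.00 |
| 3, chloroquine arm, slower half | 6.0% | 1.05 |
| 6, chloroquine arm, slower half | 7.2% | 1.11 |
| 8, chloroquine arm, slower half | 9.3% | 1.15 |
| 6, control arm, slower half | 6.7% | 0.91 |

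The shift is in one direction. With 3 and 6 excluded from the chloroquine arm, rejections in its favour were 4.7% and 6.6%, against a nominal 2.5%.

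**4. Whether censoring repairs it.** The log-rank numerator is the sum over event times t_j of d_1j − d_j × n_1j / n_j, where n_j counts patients still at risk at t_j. A patient censored at time 0 is in no n_j and contributes nothing, and the same holds for the Cox partial likelihood. A check over 2,000 simulated trials found a difference of exactly 0 between excluding such patients and censoring them at time 0. The error returned to about 5% only when their recovery times were observed.

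**5. Time origin.** A patient who never takes the drug has no start time under the definition in the plan, so cannot enter an all-randomised analysis until the origin is moved.

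**6. Rates.** If 3 of 56 patients in an arm are excluded and would count as non-successes, the success rate in that arm is inflated by a factor of 56/53 = 1.057.

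**The case against.** The best defence is that the excluded group may be very small. The footnote to Table 1 lists D1 to D7 separately, so lacking every post-dose evaluation would take a very early exit. Anyone who leaves after one evaluation is already in the set and can be censored. This stands, and it is why the effect is probably small.

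Three stronger readings are tempting, and the document does not support them.

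- A reader might take the 5% drop-out as the plan's estimate of this loss. It is general drop-out in both arms and is not stated to occur before dosing or evaluation.
- A reader might expect a large error inflation. Removing from one arm 3 or 6 patients whose recovery would take more than 14 days gives roughly 8% and 15%, and removing the 3 slowest gives 15.7%. These patterns select on an outcome unknown when the patient leaves, so they are not expected magnitudes.
- A reader might infer that a dosed patient who dies drops out of the safety set. A death is itself post-dose safety information: the Definitions count fatal events as SAEs, and Safety assessment collects all AEs. The wording is a problem only for a dosed patient who leaves with no safety contact.

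It could also be said that an article condenses the protocol. But the definition is stated here, not left out.

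**Conclusion.** The concern holds in a limited form. The label is wrong however many patients are excluded, and no all-randomised efficacy analysis is described. Bias is possible because exclusion can depend on the arm, but it also needs dependence on prognosis. The document does not show that this will happen or how large it would be. Losses that are random, or alike in both arms and moderately selected, gave no bias in the simulation. Three to six moderately selected losses in one arm gave about 6% to 7% error and HR 1.05 to 1.11 under no effect, all on an assumed pattern. The point should be fixed, but it does not by itself undermine the trial.

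**What to change.** 1. Define ITT as all randomised patients, analysed in the assigned arm.
2. Start the primary clock at randomisation, and reconcile the Definitions and Sample size sections, which start it at study drug.
3. Keep patients who refuse or stop the drug on the scheduled assessments to day 28 where they consent, and censor only true losses.
4. Because censoring at time 0 equals exclusion, add a sensitivity analysis that counts patients with no post-baseline data as not recovered at day 28.
5. Use all randomised patients as the denominator of the treatment success rate.
6. Report exclusions, with reasons, by arm.
7. Keep the present set as a sensitivity analysis, renamed modified ITT.
8. Define the safety set as everyone who took at least one dose, without the post-dose-data condition.

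The cost is a few sentences, continued follow-up of the few who leave treatment, and a slightly diluted effect estimate. The stated 112 patients need not change. If some patients have already left without follow-up, item 3 cannot be recovered for them, but the other items can still be put in place before database lock.

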**Table 1 Tab1:**
[figure not shown]
The schedule of treatments and data collection

The *SOFA (Sequential Organ Failure Assessment) score* predicts mortality risk for patients in the intensive care unit based on laboratory results and clinical data^1^

*Coagulation index*: *PT* prothrombin time, *APTT* activated partial prothrombin time, Fib fibrinogen, *D-Dimer* D-dimer, *PLT* platelet count

*Inflammatory factors*: various cytokines involved in inflammation, such as interleukin (IL)-6, IL-10, tumor necrosis factor (TNF)-α, etc.

*PCT (procalcitonin)*: a protein that increases when severe bacterial, fungal, and parasitic infections, sepsis, and multiple organ failure occur

− D0: before the research; D0: start of the research; D1: 1st day of the research; D2: 2nd day of the research; D3: 3rd day of the research; D4: 4th day of the research; D5: 5th day of the research; D6: 6th day of the research; D7: 7th day of the research; D10: 10th day of the research; D14: 14th day of the research; D21: 21st day of the research; D28: 28th day of the research; D29: after the research

References:

1 Medlej K. Calculated decisions: sequential organ failure assessment (SOFA) score. *Emerg Med Pract* 2018;20:CD1-CD2.

Researchers will evaluate treatment adherence during each visit. If a scheduled visit is delayed or cancelled, the research team will contact the participant at once. No treatment or intervention is prohibited for any of the participants.

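### The per-protocol set requires every planned visit through day 28, so the secondary per-protocol hazard ratio depends on attendance after randomization and can be biased in either direction

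*Protocol article*

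**What the plan says.** Under Statistical analysis, the protocol article has the efficacy outcomes "analyzed based on both intention-to-treat (ITT) and per-protocol (PP) approaches". It then ranks the two analyses, in these terms: "with a primary consideration for ITT results. A PP analysis will be performed secondarily". The PP set is taken from ITT members, who must "receive one study drug at least once and have post-dose evaluation data". Two further conditions apply. The first admits only "those who completed all planned visits". The second concerns other treatment and admits only "those who did not receive and use drugs or treatments that may affect the evaluation of efficacy during the study".

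The legend to Table 1 shows how far the visits extend: "D21: 21st day of the research; D28: 28th day of the research; D29: after the research". For a missed visit the article says only this: "If a scheduled visit is delayed or cancelled, the research team will contact the participant at once". It states no exemption from the visit condition for patients who have recovered, been discharged, worsened or died. The Setting section adds: "All participants can withdraw their consent at any time during the trial".

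The Design section caps treatment at 10 days. The Sample size section assumes median recovery at 8 days (control) and 4 days (chloroquine). The primary outcome is time to clinical recovery, compared by log-rank test and Cox model.

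**The concern.** Whether a patient completes every visit is known only at the end of follow-up, about 18 days after the last possible treatment day and, for most patients, after the primary event. The condition therefore selects on the future. A patient treated as planned, with recovery observed on day 5, is removed for missing day 21. A patient who dies or withdraws on day 9 cannot satisfy the condition and is deleted, although a time-to-event analysis could use the follow-up to day 9.

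The condition also misses what a PP set is meant to capture. One criterion is attendance and the other is concomitant treatment; neither asks whether the allocated drug was taken, although adherence is evaluated at each visit.

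In an open-label trial, attendance can plausibly depend on both arm and outcome. If it does, the PP result may agree or disagree with ITT because of who came back, not because of what the drugs did.

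**Working it through.** **Design figures.** The article gives no size for the PP set, so its design figures are checked first. With 78 events, HR 2 and two-sided 5%, power = Φ(√78 × ln 2 / 2 − 1.96) = Φ(3.06 − 1.96) = Φ(1.10) = 0.865. This is consistent with the stated 85%, read as power.

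**Model.** Recovery times are exponential with the article's medians (8 and 4 days, or 8 and 8 under no effect), censored at day 28, 1:1 allocation. All withdrawal and missed-visit rates are assumptions, because the article gives none by arm or by outcome.

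**Mechanism A: leaving before recovery, true HR 1.** A stated share of each arm is prone to leave at a uniform time on days 2 to 14 and does so if not yet recovered. Leaving time is independent of recovery time. The all-patient analysis censors leavers; the PP analysis deletes them.

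| Prone to leave, control / chloroquine | All-patient HR | PP HR (Cox) |
|---|---|---|
| 5% / 5% | 1.00 | 1.00 |
| 5% / 20% | 1.00 | about 1.06 to 1.07 |
| 5% / 35% | 1.00 | about 1.14 to 1.17 |
| 35% / 5% | 1.00 | about 0.86 to 0.87 |

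The ranges cover fits in very large samples and averages over trials of 56 per arm. At 5% / 35% the PP log-rank test rejects in about 10% to 11% of trials, against about 5% with all patients. Leavers are disproportionately slow to recover, so deleting them makes their arm look faster.

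**Mechanism B: recovered patients miss a later visit, true HR 2, same rule in both arms.** Share recovered by day 10:

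- control: 1 − 2^(−10/8) = 0.580
- chloroquine: 1 − 2^(−10/4) = 0.823
- average: 0.701

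If 30% of these miss a later visit, 0.3 × 0.701 = 21% of patients are dropped (about 24 of 112). If 50% do, 0.5 × 0.701 = 35% (about 39 of 112). Adding 5% prone to leave in each arm raises the upper figure to about 37%. The Cox HR moves from 2.00 to about 2.1 (30%) and 2.2 (50%). No difference in behaviour between arms is needed, because more chloroquine patients recover early. Under a true null, a mechanism tied to recovery identically in both arms leaves the HR at 1.00.

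**Other mechanisms.** With true HR 2, removing half of those not recovered by day 28 in both arms gives 1.87. One-arm mechanisms give 1.81 to 2.18. Purely random loss of 5% or 20% changes nothing.

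**Estimator.** Under mechanism B the one-step Peto estimator gives 2.27 to 2.41, but it already gives 2.09 in all patients when the truth is 2.0. The article specifies Cox, so the Cox figures apply.

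**The case against.** The strongest reply is that the article makes ITT primary and PP secondary, states no decision rule that needs the two to agree, and makes no non-inferiority claim. That stands: the visit condition does not enter the ITT analysis.

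Bias is also conditional. Attendance must be related to recovery and, under a true null, must differ by arm. The article shows neither. Its only relevant figure is a 5% drop-out rate in both groups, and 5% prone to leave in each arm gives no bias. The 5% / 35% contrast is an illustration at seven times that rate in one arm.

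A reader might infer that the rule will favour chloroquine or produce a false positive. The documents do not support this: reversing the arms reverses the direction. In mechanism B the smaller set also costs power. In trials of 56 per arm, with 5% prone to leave in each, the rejection rate falls from about 93% to 88% to 90%.

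A reader might also infer that the PP set will nearly vanish. The pair of 112 patients and 78 events fits a drop-out of 5% per day, which would leave 112 × 0.95^28 ≈ 27 patients at day 28. The article states no time unit, and 5% overall would leave up to 112 × 0.95 ≈ 106, so no PP set size can be asserted.

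Finally, a full protocol or analysis plan may define planned visits more narrowly or bring adherence into PP. That is possible, but the article states a definite rule without an exemption, so this goes beyond a detail left out. The second PP condition also filters on events after randomization and does not rescue the first.

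**Conclusion.** The point holds as a defect in the definition of a secondary analysis set. Requiring all visits to day 28 conditions PP membership on attendance after randomization, discards recoveries already observed, deletes patients who could be censored, and does not measure drug adherence. The PP comparison can be biased in either direction.

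Under the assumed rates the size is modest to moderate: about 0.86 to 1.17 around a true HR of 1, and about 2.1 to 2.2 for a true HR of 2 when early recoverers skip later visits, with a fifth to over a third of patients lost. Both ranges rest on exponential recovery times and on attendance rates that the article does not give. It would be wrong to say that bias is certain, that its direction is known, or that the trial's primary conclusion is at risk.

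**What to change.** Delete the visit-completion condition. Define PP by no major eligibility violation and by adherence to the allocated study drug up to the earliest of recovery, end of planned treatment, death or last assessment. Keep patients who miss later visits: use their recovery date if reached, and otherwise censor at the last assessment.

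The cost is a wording change, best made before the data are analysed. Adherence is already evaluated at each visit, so no new data are needed.

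The fix is partial. Patients who stop the drug when they withdraw early are still excluded. In mechanism A at 5% / 35%, about 77% of those who leave before recovery do so before day 10. Excluding them still gives an HR of about 1.08 to 1.09 under no effect, with about 7% rejection. PP should therefore be reported only as supportive of ITT, with the number and reasons for exclusion by arm.

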### Efficacy outcomes

Comparisons will be performed using two-sided tests with a statistical significance level of 5% unless stated otherwise.

